### Dissemination

To realize TCALL’s vision of a nationwide rollout, respective dissemination activities are necessary. TCALL’s communication and dissemination strategy includes an identification of relevant stakeholders (Table 3) for TCALL’s (external) scientific communication and the corresponding communication goals.

Persons in need of care and their relatives are primarily interested in an increase in the quality of care and the quality of life for residents, which is to be achieved through technical and organizational innovations and human resources development, resulting from the close integration of science and practice. Nursing staff benefit from TCALL as the innovations make everyday practice easier. Moreover, education and training methods and tools will be improved. For service providers and health insurance companies, TCALLs results of the health economic evaluation may be interesting. With respect to LTC and health policy, the focus is on the prospect of both more efficient and more effective structures and processes in care provision. From a scientific perspective, TCALL offers an excellent opportunity to analyze selected innovations during their application in everyday care.

**Table 3 Tab3:** Overview stakeholders

Stakeholders
Persons in need of long-term care
Care-givers
People working in education of care-givers (e.g. nursing trainer)
Service providers
Financing agencies (e.g. LTC funds)
Politicians/Political institutions
Researchers (in nursing science)
Media
Other providers (doctors, therapists)

These nine stakeholders require target group-specific communication measures. In addition, certain actors have a particularly important role to play in the realization of the project vision in the form of a sustainable (nationwide) rollout of TCALL. These actors are divided into two groups accordingly, namely the group of multipliers and the group of decision-makers. The multipliers are separate actors from the individual TCALL interest groups who pass on project content to other interested parties, multipliers and decision-makers and, if necessary, also actively convince them to support the initiative. This group of stakeholders is able to support the strategy implementation process. This group includes, for example, influential organizational actors such as interest groups in the healthcare sector.

Decision-makers are actors with great potential for political action in health policy or care practice (e.g. political institutions, politicians; other actors involved in financing the project such as health insurance companies or their associations). The focus of addressing decision-makers is on increasing both the quality of care and cost efficiency.

Before multipliers and decision-makers can be specifically addressed through communication activities, they must be identified. In the course, a database of relevant persons is built up and continuously expanded. The strategic TCALL network created in this way is an important component of the communication and dissemination strategy of the TCALL initiative.

## Discussion

### Summary and placement in the literature

LTC faces different challenges in the next years, including the realization and connectivity to research, especially to digitalization and the growing decline in staff. Making the nursing profession attractive again, especially in LTC, and creating an innovative transfer structure between science and practice working in both ways is the primary objective of TCALL with the development and implementation of ATNH in the federal state of Bremen, and finally in Germany. Other countries, like the USA or Netherlands, have already set off approaches to renew LTC and promote exchange between science and practice a long time ago. The Living Lab in Ageing and Long-Term Care by Maastricht University in the Netherlands successfully created a collaboration between scientists, care providers, and educators in LTC in order to improve quality of life of older people and their families, quality of care and quality of work for nursing staff. This collaboration has been established for 25 years now, and main factors for success are Linking Pins and interdisciplinary approaches [5]. TCALL comes into these factors by introducing TIAs and interdisciplinary supervision. Similar work and goals can be found in Teaching Nursing Homes in the USA or Norway where partnerships between service and academia include benchmarks of nursing home professional learning environment, interdisciplinary education and practice as well as research and dissemination of evidence-based practices. Teaching Nursing Homes in the USA started in the 1980s in order to improve resident outcomes and to foster research among other things. Few schools of nursing homes and medicine have maintained this model over the past 15 years. However, up to date, there has been little research concerning effectiveness in terms of whether Teaching Nursing Homes can potentially enhance research training opportunities in the health professions and contribute significantly to better outcomes for residents [38]. TCALL addresses exactly this point and takes a formative and summative evaluation into account. In addition, the course is set for national expansion by asking and clarifying legal questions during the development and implementation of ATNH.

### Strengths and limitations

The vision of the TCALL initiative is to restructure the provision of care by strengthening the transfer path between science and practice. A great advantage and chance for success is the long duration of the initiative, up to nine years, which enables an adequate testing of the different innovations, time for adaption and an accompanying implementation. This is nearly never given in Germany, especially in research projects. This long period holds great potential to really improve care, the quality of care, working conditions and the quality of life. A lot of things which are often not done in research due to time or cost limits, like e.g., several process adaptions, is possible in TCALL. Furthermore, the close exchange with employees of the ATNH and their management provides important insights into everyday practice and leads to development of innovations which are really needed and therefore more accepted by employees and are directly tailored to their working conditions. In many studies the implementation of innovations fails as nursing home staff has no capacities to integrate these innovations in everyday routine. The new created decentralized learning infrastructure and the TIAs, funded by the TCALL initiative, are the additional resource needed to overcome this problem. The TIAs are a clear strength as they act as an interface between science and practice. There is often massive criticism because practice partners are not involved in the process, or developments from research are not relevant to the day-to-day work of nursing staff in long-term care. The explicit mission of the TIAs is to gain and share insights and observations from the field so that these important aspects of employees and ATNH can be taken into account. This will lead to improved processes concerning the selection of (technical) innovations and their implementation.

Another strength is that the dissemination strategies for consolidation of sustainable ATNH and for a nationwide rollout are thought of from the beginning with the idea to establish a publicly funded and legally anchored concept for ATNH in Germany after nine years, which will be a great milestone in nursing science and nursing practice. If successful, the concept for ATNH could even be transferred to and implemented in other European and Western Countries to meet the demand of high-quality care with a simultaneous improvement in working conditions to reach a high attractiveness of the nursing profession.

There are few limitations in this evaluation. As the planned interventions in the TCALL initiative entail massive changes, the intervention facilities were chosen on a self-selective basis and include only nursing homes which already offer a high quality in care and high work standards (convenience sample). This might have an impact on implementation, results and overall success or failure. Moreover, a convenience sample indicates that the sample may not be typical of the population as a whole and the findings may not apply to other groups [39]. Another limitation is that at this stage, it remains unclear, if transferability to other nursing homes is possible or whether major adjustments are required.

Data collection concerning residents is carried out by nurses which results in an additional workload for them which in turn may lead to refusal or lack of commitment to the study. It can also affect data collection, which carries the risk of a high dropout rate.

The evaluation is performed by the study team itself, in detail by the coordination team, and not externally. The advantage is that the team is very familiar with the complex intervention and its implementation and therefore the interpretation of results is easier and can be used for process management and development directly. However, the self-evaluation lacks external proof of effectiveness, particularly with regard to the generalizability of the results for wider dissemination [40].

## Trial status

Recruitment for the control group is ongoing, data collection for t0 is ongoing at date of submission.

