#### Data collection

The study protocol follows the SPIRIT reporting guidelines for study protocols for clinical trials. Outcomes will be measured with reliable, valid and pretested instruments (Table 1). Most used questionnaires are free to use and do not need any license except for “The Neuropsychiatric Inventory Nursing Home Version (NPI-NH)” and the *“*Adult Social Care Outcomes Toolkit (ASCOT-SCT4)”. Licenses in both cases were obtained and permission for use is confirmed. Ethical approval was confirmed by the ethics committee of the German Society of Nursing Science in October 4th, 2024. Baseline data collection in the intervention group started in November 11th, 2024 and is ongoing, follow-up data collection continues at six-month intervals, and the end of the first study phase is planned for 2027. Questionnaires for employees and residents are completed digitally, with the exception of the Adult Social Care Outcomes Toolkit (ASCOT-SCT4) [21], which is paper-based. Data collection of residents’ files, structural data of institutions and data from quality audits will be retrieved by the staff of the University of Bremen and the City University of Applied Sciences in Bremen. All data collection will take place in the intervention nursing homes and matched control groups. Data analysis is pseudonymized.

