### Evaluation

#### Study design and participants

The basic methodology is a systemic evaluation approach [22], which combines both qualitative and quantitative research elements. The intended restructuring in the nursing homes can affect different, sometimes ethically relevant impact dimensions such as the quality of care for highly vulnerable people but also working conditions and processes. These dimensions will be captured using quantitative (standardized questionnaires) and qualitative methods such as focus groups and research diaries to gain further insights from residents, employees, nursing home management and TIAs concerning the implementation process of the several elements within the TCALL initiative (Fig. 4). For a successful implementation it is essential to fully understand rejecting or driving behaviors of all participating members in order to adapt the implementation process. This can lead to minor or major adaptions in single or multiple parts of the TCALL initiative. Additionally, qualitative methods support the participative, co-creative approach and will ensure that all participants (but especially the employees) feel valued and help changing and shaping the restructuring processes in nursing homes. In contrast to laboratory conditions, it is of great importance to address essential disruptive factors in everyday care immediately in order not to jeopardize the initiative and to keep employees and management motivated. An explanatory sequential mixed-methods design with an embedded quasi-experimental long-term study is used for the evaluation of this complex intervention to ensure that aspects of the quantitative results are interpreted correctly and to have reference points when contradictory results occur [23]. The study design also takes into account that confounding factors can influence the assessment of the outcomes. An important factor here has been the pandemic situation of the last few years, which has had a major impact on the care situation in LTC [24, 25] as well as changes in care policy, such as the implementation of new staffing ratios and their financing (Paragraph 113c of the German Social Code, Part 11). In order to avoid bias in the evaluation of the initiative, which may be associated with future changes, a matched control group is integrated into the evaluation.

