#### Summative evaluation

As briefly described above, the evaluation focuses on different outcomes at two different levels: (i) employees and (ii) residents, but on non-intended effects as well. Changes due to the complex intervention are expected in job satisfaction of employees in the ATNH compared to control nursing homes. Additionally, there are several changes expected for employees concerning organizational commitment, mental workload or sickness rates and the use of temporary employment agencies. For residents it is expected that the complex intervention will alter quality of care in the ATNH compared to control nursing homes. Further outcomes include the number of nursing home-sensitive hospital diagnoses and apathy symptoms. A full list of all outcomes and instruments is shown in Table 1. All outcomes are measured at baseline, at multiple follow-ups at six-month intervals and at the end of the study (in this case the end of the first phase in 2027). Outcomes are measured via (standardized) questionnaires and/or external assessment by a nurse, and an analysis of resident files and routine data of nursing homes. Sociodemographic data of employees and residents will be collected and analyzed. A secondary data analysis of obligatory quality indicators and external quality audits will be conducted. These internal and external quality indicators (see supplementary material additional file 1) are mandatory in Germany since 2022 and are reported publicly semi-annually. Internal quality indicators include 15 self-assessed items regarding three themes collected by nursing homes and their employees. External quality audits are structured in six themes with 24 items and are collected from assessors and evaluators on behalf of the LTC insurance fund (e.g., Medizinische Dienste/medicproof GmbH).

**Table 1 Tab1:** Overview of outcome and instruments for employees and residents

Outcome	Instruments (Source)

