#### Statistical analysis

The statistical analysis examines the changes in the outcomes in both groups, i.e., employees and residents, in t0 compared to t1-t6 and checks whether these changes differ between the intervention and control groups (difference-in-difference approach). Via correlation analyses we also analyze correlations between different outcome measures as e.g., job satisfaction and quality of care. Confounders will be controlled via regression analyses.

Information conducted within the formative evaluation especially from focus groups will be analyzed descriptively. Click rates and social media views are counted and analyzed with several digital analysis tools and programs to evaluate the dissemination activities.

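### Any t0 after 31 December 2024 cannot yield t1-t6 by the end of 2027, and with control recruitment still open the difference-in-differences is not tied to common calendar periods

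*Protocol article*

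**What the plan says.** The Data collection section fixes three elements of the schedule. On the start it says "Baseline data collection in the intervention group started in November 11th, 2024 and is ongoing", on spacing "follow-up data collection continues at six-month intervals", and on the finish "the end of the first study phase is planned for 2027". It adds that collection covers both the intervention and the matched control homes. The Summative evaluation section repeats the scheme and adds a closing measurement: "All outcomes are measured at baseline, at multiple follow-ups at six-month intervals and at the end of the study", the end of the study here being the end of the first phase.

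The Statistical analysis section examines changes "in t0 compared to t1-t6 and checks whether these changes differ between the intervention and control groups", by difference-in-differences. The purpose of the control homes is given under Study design and participants, after the pandemic and the new staffing ratios are named as external influences: "In order to avoid bias in the evaluation of the initiative, which may be associated with future changes, a matched control group is integrated".

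On progress, the Recruitment section says that control recruitment is still under way, and Trial status says "Recruitment for the control group is ongoing, data collection for t0 is ongoing at date of submission". The article gives neither a submission date nor a control baseline date, and it does not say whether t0 to t6 are common calendar waves or are counted from each home's own baseline.

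**The concern.** The schedule fits only if baseline is finished almost at once, and control homes were still being sought after intervention baseline had opened. Two things are at stake.

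- **The number of waves.** A home or participant who starts late cannot supply the six follow-ups that the analysis names.
- **What the contrast removes.** A concurrent control group cancels a policy or staffing change only if both groups are observed before and after it. With unequal baselines and alignment by visit number, a change that falls between the two baselines is counted in one group only. That is the bias the control group was added to prevent.

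**Working it through.** **Inputs.** Intervention t0 from 11 November 2024, six-month spacing and a phase end in 2027 (Data collection); six follow-ups (Statistical analysis). No day is given for the phase end, so 31 December 2027 is taken as the latest possible date.

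**1. The plan's own schedule.** With t_k = t0 + 6k months, a participant measured on 11 November 2024 has t1 on 11 May 2025, t2 on 11 November 2025, t3 on 11 May 2026, t4 on 11 November 2026, t5 on 11 May 2027 and t6 on 11 November 2027. All six fit. Slack to 31 December 2027: 19 + 31 = 50 days.

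**2. Latest workable t0.** 31 December 2027 minus 6 × 6 = 36 months is 31 December 2024. That is 50 days after intervention baseline opened and 22 days after the registration date in the abstract (9 December 2024).

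**3. Waves that fit by t0 date** (dates after 2024 are assumptions):

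| t0 | Half-yearly follow-ups by 31 Dec 2027 |
|---|---|
| up to 31 Dec 2024 | 6 |
| Jan-Jun 2025 | 5 |
| Jul-Dec 2025 | 4 |
| Jan-Jun 2026 | 3 |

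A control t0 of 11 May 2025 lags the intervention start by 6 months and would put t6 on 11 May 2028. A t0 of 11 November 2025 lags by 12 months. The same limit applies to intervention participants first measured after 2024, since intervention t0 was also still open.

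**4. When was the text written?** It quotes the registration of 9 December 2024, so it is no older than that. The section on aims and structure speaks of sub-projects begun in 2024 in the past tense and of one still planned for the end of 2025. That points to 2025, hence to at least some control baselines after 2024. It is an inference, not a stated date.

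**5. Effect on the difference-in-differences if t is counted from each home's own baseline.** Let g(c) be the calendar-time effect common to both groups, a the intervention t0 and L the control lag in months. At wave k the estimate carries

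B_k = [g(a + 6k) − g(a)] − [g(a + L + 6k) − g(a + L)].

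- Linear trend with slope b: B_k = 6kb − 6kb = 0.
- Lasting step of size s after a and before a + L, with wave k of the intervention group after the step: B_k = (s − 0) − (s − s) = s.
- Lasting step after both a + L and a + 6k, but before a + L + 6k: B_k = (0 − 0) − (s − 0) = −s.

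A smooth common trend therefore does no harm, but a lasting one-off shock in the gap enters at full size.

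**6. If t means common calendar waves.** The periods align, but a late control home has no observation at a. For questionnaires the control change from t0 cannot then be formed.

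**The case against.** The strongest reply is that this is a conditional problem. Ongoing recruitment does not exclude that one or two control homes had already joined, no control date is given, and intervention baseline was itself still open, so the lag may be short. The indexing of waves is commonly settled in an analysis plan that is not shown. All of this stands as a limit on the claim. It does not remove it: under either meaning of t, one stated element fails for a late control home, either the calendar match or the concurrent t0.

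Three stronger readings are tempting, and the documents do not support them.

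- A reader might infer that the six waves do not fit at all. They do for participants measured by the end of 2024.
- A reader might infer that control homes start long after the intervention homes. The length of the lag is not documented.
- A reader might infer that the end-of-phase contrast will be missing for controls. The Summative evaluation section already plans a measurement at the end of the phase, so late controls lose intermediate waves. If that measurement serves as t6, a control t0 up to about mid-2025 could supply t1-t5 plus t6, though over a shorter span than the 36 months in the intervention group.

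It is also fair to say that the main resident outcome is largely protected. Quality of care rests on mandatory indicators published half-yearly, and routine data are gathered regardless of the study, so both can be aligned by calendar date afterwards. The exposure lies mainly with the questionnaires, which include job satisfaction, the main employee outcome.

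**Conclusion.** The point holds in this form. A t0 after 31 December 2024 cannot yield t1-t6 at six-month spacing by the end of 2027; five, four or three waves fit, depending on the half-year of t0. This is calendar arithmetic on the article's own dates and is certain, given 31 December 2027 as the latest end. That some control baselines fall after 2024 is a strong inference.

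The bias is conditional. It needs t to be counted from own baseline and a lasting shock inside the lag, and it then equals the shock in full; a common linear trend cancels. With common calendar waves the cost is instead a missing concurrent questionnaire baseline in late control homes. The documents do not support saying that bias has been shown or that the final contrast is lost.

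**What to change.** 1. Index every observation by calendar half-year and fit the difference-in-differences with calendar-period effects.
2. Use the end-of-phase measurement in 2027, which is already planned, as the common final wave.
3. Limit the t1-t6 statement to homes and participants whose t0 allows it.
4. For published quality indicators and routine data, extract control values back to the calendar half-year of intervention t0, so that these outcomes keep a concurrent baseline.
5. For questionnaire outcomes, report the actual baseline dates and the lag between groups, and keep the intervention t0 data. Use the first half-year observed in both groups as the reference only in a sensitivity analysis. The first sub-projects began in December 2023 and January 2024, so a later reference moves further into the exposed period and may bias towards no effect.

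The cost is a wording change, some extra data extraction in three control homes, and fewer fully concurrent questionnaire waves. No re-indexing can recreate a control questionnaire baseline that was not collected, so the dates of remaining control visits should be aligned now.
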